## Abstract

**Background:**

Patients with cancer often endure substantial symptoms and treatment toxicities leading to high healthcare utilization, including hospitalizations and emergency department visits, throughout the continuum of their illness. Innovative oncology care models are needed to improve patient outcomes and reduce their healthcare utilization. Using a novel hospital at home care platform, we developed a Supportive Oncology Care at Home intervention to address the needs of patients with cancer.

**Methods:**

We are conducting three trials to delineate the role of Supportive Oncology Care at Home for patients with cancer. The Supportive Oncology Care at Home intervention includes: (1) a hospital at home care model for symptom assessment and management; (2) remote monitoring of daily patient-reported symptoms, vital signs, and body weight; and (3) structured communication with the oncology team. Our first study is a randomized controlled trial to test the efficacy of Supportive Oncology Care at Home versus standard oncology care for improving healthcare utilization, cancer treatment interruptions, and patient-reported outcomes in patients with cancer receiving definitive treatment of their cancer. Participants include adult patients with gastrointestinal and head and neck cancer, as well as lymphoma, receiving definitive treatment (e.g., treatment with curative intent). The second study is a single-arm trial assessing the feasibility and acceptability of the Supportive Oncology Care at Home intervention for hospitalized patients with advanced cancer. Eligible participants include adult patients with incurable cancer who are admitted with an unplanned hospitalization. The third study is a single-arm trial assessing the feasibility and acceptability of the Supportive Oncology Care at Home intervention to enhance the end-of-life care for patients with advanced hematologic malignancies. Eligible participants include adult patients with relapsed or refractory hematologic malignancy receiving palliative therapy or supportive care alone.

**Discussion:**

These studies are approved by the Dana-Farber/Harvard Cancer Center Institutional Review Board and are being conducted in accordance with the Consolidated Standards of Reporting Trials statement for non-pharmacological trials. This work has the potential to transform the paradigm of care for patients with cancer by providing them with the necessary support at home to improve their health outcomes and care delivery.

**Trial registrations:**

NCT04544046, NCT04637035, NCT04690205.

## Background

Patients with cancer endure a serious, life-threatening diagnosis and often receive intensive therapies that result in substantial side-effects and toxicities such as nausea, vomiting, diarrhea, fatigue, and infectious complications [1–7]. These toxicities commonly lead to high healthcare utilization, including frequent emergency department (ED) visits and prolonged hospitalizations, which contribute to the rising costs of cancer care, impaired patient quality of life (QOL), and morbidity related to treatment [1–16]. Notably, patients with advanced cancer experience multiple ED visits during the first year of diagnosis, with over half of these visits resulting in an inpatient hospitalization [4–6, 17]. Moreover, over 40% of hospitalized patients with advanced cancer have a hospital readmission within 90 days of discharge and a substantial proportion of these hospitalizations are potentially avoidable [13–15]. Thus, there is a critical need to develop novel healthcare delivery models to enhance the experience of patients with cancer, improve patient outcomes, and reduce their healthcare utilization.

The hospital at home care model offers an alternative approach to treating patients in need of emergent or inpatient acute care in their homes, with many studies demonstrating its safety and efficacy, albeit in the general medical population [18–30]. Hospital at home entails the provision of comprehensive medical care, such as vital sign monitoring, clinician home visits, intravenous therapies, physical therapy, and nutritional services, coupled with a rapid response to address the needs of acutely ill patients in their home [21, 28–30]. Prior research demonstrates that hospital at home care models improve patient outcomes, such as satisfaction with care and functional status, while decreasing healthcare utilization and costs in patients with chronic medical conditions, such as congestive heart failure and chronic obstructive lung disease [18–30]. A recent study of a hospital at home care model replacing acute hospitalizations for patients with cancer has also shown a reduction in healthcare utilization and cost of care [31]. However, hospital at home interventions have not been tested as longitudinal care models for patients with cancer to improve their overall QOL and care throughout their illness continuum. Thus, hospital at home longitudinal care models represent an innovative approach with the potential to improve clinical outcomes, optimize cancer care delivery, and reduce healthcare utilization among patients with cancer.

Symptom monitoring interventions in oncology have demonstrated encouraging efficacy in reducing patients’ symptom burden, improving their QOL, and decreasing healthcare utilization [32–35]. For example, randomized trials of symptom monitoring interventions in ambulatory patients with cancer have shown better symptom control, decreased use of hospital-level care, and improved survival for those receiving the intervention compared to usual care [32–37]. Therefore, integrating symptom monitoring with hospital at home care models provides a novel solution to help optimize the care of patients with cancer, enhance their clinical outcomes, and reduce their use of healthcare services.

Patients with cancer experience immense toxicities and a substantial hospitalization burden, and we therefore developed a novel Supportive Oncology Care at Home program to address patients’ symptoms and clinical needs, improve their QOL and care experience, and reduce their use of hospital-level care. The Supportive Oncology Care at Home intervention includes the following: (1) hospital at home care model for symptom assessment and management; (2) remote monitoring of patient-reported symptoms, vital signs, and body weight; and (3) structured communication with the oncology team. We are currently conducting three trials to delineate the role of Supportive Oncology Care at Home in addressing the needs of patients with cancer throughout the continuum of their illness.

## Methods/design

### The supportive oncology care at home intervention

We developed the Supportive Oncology Care at Home intervention with input from oncology nurses, nurse practitioners, oncologists, and palliative care clinicians who specialize in caring for patients with cancer (Fig. 1). The Supportive Oncology Care at Home intervention is provided by a dedicated, trained Medically Home care team (physicians, advance practice clinicians, and nurses) in collaboration and partnership with the primary oncology team. Medically Home is available 24-h a day to provide home assessments and deliver needed interventions at home, including radiology studies, laboratory tests, intravenous hydration, medications, and rapid response, as needed. Additional services including physical and occupational therapy, nutrition, home health aides, durable medical equipment, and social work are also available to help meet the needs of patients and their families within their home. Patients receive a Medically Home technology platform that supports virtual care, including video visits, patient data transmission, and deployment of home-based services.

**Fig. 1 Fig1:**
[figure not shown]
Supportive Oncology Care at Home Intervention

Patients receiving the intervention first have an initial one-hour visit in their home with the Medically Home team. During this visit, a trained Medically Home clinician reviews the services included in the program, performs a physical exam, assesses the patient’s home safety, and educates the patient and caregivers on the use of technology provided (e.g., tablet computer, wireless phone, and vital sign monitoring equipment). The Medically Home care team provides: (1) monitoring of patient-reported symptoms using the Edmonton Symptom Assessment System (ESAS), vital signs, and body weight measurement with appropriate triggers for phone calls and home visits by Medically Home based on a clinician-derived algorithm; (2) clinician home visits for medical assessment and management as needed; and (3) regular communication with oncology clinicians regarding care delivered at home to ensure continuity of care. Patient reports of their symptoms and vital signs are monitored in real-time and reviewed by Medically Home clinicians to initiate prompt responses. Using data from the symptom, vital sign, and body weight monitoring, the intervention contains detailed algorithms indicating when the Medically Home team should call the patient to check-in. For example, Medically Home can contact the patient regarding any of the following: (1) if the patient does not complete their daily symptom assessment by 1:00 pm; (2) any ESAS symptom score ≥ 7; (3) an increase in ESAS symptoms score ≥ 2 points from the previous day; (4) heart rate < 50 or > 100 beats per minute; if baseline heart rate > 100, then a 25-point increase in heart rate should result in a phone call; (5) temperature > 100.4 degrees Fahrenheit; (6) oxygen saturation < 90%; and (7) weight loss of 5 or more pounds over the prior week. If the patient has questions or concerns at any time, they can contact Medically Home directly via a 24/7 access line. The study team and Medically Home clinicians meet weekly to help ensure intervention fidelity, adherence, and utility.

### Study #1: supportive oncology care at home for patients with cancer receiving definitive treatment

#### Study design/objectives

We recently completed a pilot feasibility study assessing the role of Supportive Oncology Care at Home for patients with pancreatic cancer receiving neoadjuvant treatment [38]. Findings of this pilot demonstrated the feasibility and acceptability of the Supportive Oncology Care at Home intervention, with encouraging preliminary findings demonstrating reduced healthcare utilization in this population. Building on this work, we are currently conducting a randomized controlled trial to assess the efficacy of the Supportive Oncology Care at Home intervention for enhancing care delivery and outcomes in 300 patients with cancer receiving definitive treatment with curative intent (Fig. 2) (NCT04544046; DFCI Protocol Number:20–331). We are recruiting patients at Massachusetts General Hospital (MGH) in Boston and two MGH community affiliates (MGH Newton-Wellesley and MGH North Shore). This study is approved by the Dana-Farber/Harvard Cancer Center (DF/HCC) Institutional Review Board. Study staff received detailed training in data entry, security, storage, and management procedures for data collection.

**Fig. 2 Fig2:**
[figure not shown]
Supportive Oncology Care at Home for Patients with Cancer Receiving Definitive Treatment Consort Diagram

#### Participant selection

The study focuses on oncology populations receiving definitive treatment who have high-risk for side effects, treatment interruptions, ED visits, and hospitalizations during treatment. To be eligible, patients must be: (1) age 18 or older; (2) receiving definitive treatment (i.e., chemotherapy and/or chemoradiation with curative intent) for pancreatic cancer, gastroesophageal cancer, colorectal cancer, head and neck cancer, or aggressive non-Hodgkin lymphoma; (3) within two weeks of starting treatment; (4) planning to receive care at MGH or MGH affiliate sites; (5) verbally fluent in English; and (6) residing in-state, within approximately 50 miles of MGH. Exclusion criteria include uncontrolled psychiatric or impaired cognition interfering with the patient’s ability to understand study procedures and provide informed consent based on the oncology clinician’s assessment.

#### Enrollment and randomization

We will identify patients for study participation by screening the outpatient gastrointestinal oncology, head and neck cancer, and lymphoma clinic schedules and clinical trial enrollment on a weekly basis. The study team will email the oncology clinician to request permission to approach the patient for study participation. If the oncology clinician has no objections, the study team will approach the patient in-person or over the phone and obtain informed consent. Patients will then be asked to complete baseline assessment and they will be registered and randomized using a central randomization office. Randomization will be 1:1, stratified by cancer type (gastroesophageal vs. pancreatic vs. rectal vs. head and neck vs. lymphoma) to the Supportive Oncology Care at Home intervention described above (Fig. 1) versus usual care (computer generated with randomly permuted blocks). Participants assigned to usual care will receive standard oncology care and attend their regular clinic visits.

#### Timeline

The duration of an individual’s active participation in the study will include their time receiving definitive treatment (i.e., neoadjuvant chemotherapy or chemoradiation treatment with curative intent) and up to 6 months following the treatment start date. For those with gastrointestinal cancer, the Supportive Oncology Care at Home intervention will continue throughout the duration of their chemotherapy treatment. For those with head and neck cancer, the intervention will continue throughout the duration of their chemoradiation treatment and until 30 days after completing treatment, given the residual symptoms experienced by this population.

#### Study outcomes

The primary endpoint of the trial is the proportion of patients requiring hospital admission or ED visit (yes vs. no) during the study period. Secondary endpoints include: (1) proportion of days patients spent outside of the hospital during the study period; (2) proportion of patients needing an urgent visit to the clinic (yes vs. no); (3) proportion of patients requiring treatment interruption (yes vs. no); (4) relative dose intensity of definitive treatment received; and (5) change in patient-reported outcomes longitudinally during the study period (up to six months after therapy initiation). Patient-reported outcomes will be collected at baseline and monthly throughout the intervention until six months post-baseline. Table 1 depicts study outcomes including the patient-reported assessments used in this trial.

**Table 1 Tab1:** Supportive Oncology Care at Home for Patients with Cancer Receiving Definitive Treatment Study Outcomes

Study Outcomes
**Health Care Utilization Outcomes**
Proportion of patients requiring a hospital admission or ED visit during the study period **(primary endpoint)**
Proportion of days patients spent outside of the hospital during the study period
Patients needing an urgent care visit (yes/no)
**Cancer treatment-related outcomes**
Patients receiving treatment interruption (yes/no)
Relative dose intensity of definitive treatment received
**Patient-reported outcomes**
Changes in symptom burden (ESAS) longitudinally throughout the study
Changes in QOL (FACT-G) longitudinally throughout the study
Changes in psychological distress (HADS/PHQ-4) longitudinally throughout the study
Changes in care satisfaction (FAMCARE) longitudinally throughout the study
Changes in ADLs (MOS) and IADLs (OARS) longitudinally throughout the study

#### Sample size calculation

The primary endpoint of the proposed study is a comparison of the proportion of patients requiring a hospital admission or ED visit during the study period between the study groups. Enrolling 300 patients, or 150 per arm, will provide > 80% power to detect a 15% difference between arms, assuming the rate in the control arm is 55% (based on our experience in the pilot study and prior published literature), with a 5% two-sided type 1 error. A 15% difference in the proportion of patients requiring a hospital admission or ED visit represents a clinically important difference, consistent with other practice-changing supportive care interventions in oncology [32, 39–41]. We had no missing data on healthcare utilization in our pilot work as these patients are receiving care at our institution, and we will use the intention-to-treat principle with all randomized subjects.

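### Study 1's stated power of more than 80% is wrong: 150 per arm for 55% versus 40% at two-sided 5% gives about 74%

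*Protocol article*

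**What the plan says.** Study 1 randomises 1:1, and its primary endpoint is binary: "The primary endpoint of the trial is the proportion of patients requiring hospital admission or ED visit (yes vs. no) during the study period". The Study 1 section "Sample size calculation" gives every input of the power calculation:

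- Size, power and control rate: 300 patients, 150 per arm, "will provide > 80% power to detect a 15% difference between arms, assuming the rate in the control arm is 55" per cent.
- Effect: a 15% difference between arms, justified by the statement that "A 15% difference in the proportion of patients requiring a hospital admission or ED visit represents a clinically important difference".
- Error rate: "with a 5% two-sided type 1 error".

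The section makes no allowance for missing outcomes. It reports no missing utilisation data in the pilot and plans an intention-to-treat analysis of everyone randomised. It mentions no adjusted analysis or other feature that would raise the power.

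**The concern.** A 15-point difference around a rate near 50% is where a binomial comparison is least powerful, and 150 per arm looks small for it at a two-sided 5% level. The calculation can be redone from the article alone, so the stated figure is either right or wrong; nothing turns on an unseen analysis plan.

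Study 1 is the only randomised efficacy trial of the three, and the figure belongs to its primary endpoint. If the trial shows no significant difference, readers will take it as evidence, with at least 80% power, against an effect the article itself calls clinically important. If the true power is lower, that reading is too confident.

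**Working it through.** **Inputs**, all from Study 1, "Sample size calculation" (1:1 allocation from "Enrollment and randomization"): n = 150 per arm, p1 = 0.55, p2 = 0.55 − 0.15 = 0.40, alpha = 0.05 two-sided (z = 1.960), no loss of outcomes.

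**Attempt to reproduce the stated power (pooled-variance z test)**

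- Mean rate = (0.55 + 0.40)/2 = 0.475.
- SE under the null = sqrt(2 × 0.475 × 0.525/150) = 0.05766.
- SE under the alternative = sqrt((0.55 × 0.45 + 0.40 × 0.60)/150) = 0.05701.
- z = (0.15 − 1.960 × 0.05766)/0.05701 = 0.649.
- Power = Φ(0.649) = **74.2%**; type II error = **25.8%**.

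The stated figure of more than 80% is not reproduced.

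**Does the choice of test matter?** Same inputs, two-sided 5%:

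| Test | Power |
|---|---|
| Pooled z | 74.2% |
| Unpooled z | 74.9% |
| Arcsine | 74.3% |
| Pearson chi-square, full enumeration | 75.9% |
| Fisher exact, full enumeration | 72.1% |
| Continuity-corrected z | 70.3% |

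None reaches 80%.

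**Does another reading of the 15% rescue it?** Pooled z, two-sided 5%:

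- An increase, 55% to 70%: 76.8%.
- A 15% relative reduction, 55% to 46.75%: 29.7%.

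**What does exceed 80%?** With the other inputs fixed, a one-sided 5% test: z = (0.15 − 1.645 × 0.05766)/0.05701 = 0.967, power 83.3%. The one-sided 5% sample size formula with continuity correction at 80% power returns exactly 150 per arm. This suggests where the number came from, but that is inference, since the article names neither test nor software.

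**What 80% power would take, two-sided 5%**

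- For 55% versus 40%: n = (1.960 × sqrt(2 × 0.475 × 0.525) + 0.842 × sqrt(0.55 × 0.45 + 0.40 × 0.60))² / 0.15² = 172.8, so 173 per arm, 346 in total (186 per arm, 372 in total, with continuity correction).
- At 150 per arm: power is 79.6% at 16.0 points and 80.1% at 16.1 points, so the detectable difference is about 16.1 points (55% versus 38.9%).

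**Would a stratified comparison close the gap?** The article gives neither stratum sizes nor stratum risks, so this assumes five equal strata and a constant 15-point difference. Each result is set against the crude figure from the same variance formula.

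| Assumed control risks | Pooled | Unpooled |
|---|---|---|
| Crude, 55% throughout | 74.2% | 74.9% |
| 45–65% across strata | 75.0% | 75.8% |
| 35–75% across strata | 77.7% | 78.4% |

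The gain is about 1 point in the first scenario and 3.5 points in the second. Both stay below 80%.

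**The case against.** The arithmetic is hard to dispute; the case on the other side concerns its weight.

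- **The gap is modest.** Power is short by about 6 points and the detectable difference moves only from 15 to 16.1 points. The type I error, the endpoint and the effect estimate are untouched, and a reported confidence interval would show what a null result excludes. All true, and the reason no redesign is asked for. It does not make the printed figure correct.
- **The cause is unknown.** A misreported input, rather than a one-sided calculation, could explain the mismatch. With 150 per arm, a 15-point reduction does have more than 80% power at control rates of about 35% or lower, or about 80% or higher. This stands as a caution about the cause. It does not help at the stated 55%.
- **The full protocol or analysis plan may already specify a stratified analysis.** That is possible, and recommending one is therefore optional. Under the scenarios above it would not bring the power to 80%, and the sample size section does not rely on it.
- **Missing outcomes should not be counted against the design.** Agreed: the article gives its reason for expecting none, and the 74% assumes none.

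**Conclusion.** The stated power is wrong as written. On the article's own inputs Study 1 has about 74% power (70% to 76% across standard two-sided tests), and a type II error of about 26% instead of less than 20%, which is 25.8/20 = 1.29 times the implied ceiling. A true 15-point effect would be missed about one time in four. The result assumes only the stated 150 per arm, 55% versus 40%, two-sided 5% and complete outcome data; it does not depend on the choice of test or the direction of the difference. That a one-sided calculation lies behind the figure is plausible but not established.

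**What to change.** Replace the power statement in Study 1, "Sample size calculation", with wording such as: *150 patients per arm provide about 74% power to detect 55% versus 40%, and 80% power to detect a difference of about 16 percentage points, with a two-sided type I error of 5%.* If the intended test level or control rate differed from what is printed, correct that input and show the calculation. The cost is one sentence and a less favourable stated power; no extra patients or data are required.

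Optionally, and unless the analysis plan already does so, compare the arms within the cancer-type randomisation strata in the primary analysis (Mantel-Haenszel or standardised risk difference). This recovers perhaps 1 to 3.5 points under the assumptions above. The strata name rectal cancer while the eligibility criteria admit colorectal cancer, so the strata should be clarified before the analysis relies on them.

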### Study #2: feasibility of delivering a supportive oncology care at home intervention for hospitalized patients with cancer

#### Study design/objectives

Hospitalized patients with advanced cancer represent a population at risk for high symptom burden and increased healthcare utilization. Elevated physical and psychological symptoms in hospitalized patients with advanced cancer are associated with increased healthcare utilization, including prolonged hospital stay and increased risk of readmissions [12, 14, 42]. We are conducting a single-arm pilot study (*N* = 30) to evaluate the feasibility and acceptability of the Supportive Oncology Care at Home intervention for recently hospitalized patients with advanced cancer and their caregivers (NCT04637035; DFCI Protocol Number:20–414). We will recruit hospitalized patients with advanced cancer from MGH. Figure 3 depicts the trial flow diagram. This study is approved by the DF/HCC Institutional Review Board.

